## Abstract

**Background:**

Thirty thousand knee replacements are performed annually in the UK. There is uncertainty as to the best surgical approach to the knee joint for knee arthroplasty. We planned a randomised controlled trial to compare a standard medial parapatellar arthrotomy with sub-vastus arthrotomy for patients undergoing primary total knee arthroplasty in terms of short and long term knee function.

**Methods:**

Patients undergoing primary total knee arthroplasty at the local NHS Trust are to be recruited into the study. Patients are to be randomised into either the subvastus or medial parapatellar approache to knee arthroplasty. The primary outcome measures will be the American Knee Society and WOMAC Scores. The secondary outcome measures will be patient based measures of EuroQol and SF-36. All outcomes will be measured pre-operatively, 1, 6, 12 and 52 weeks post-operatively. We will also review pain intensity using a pain and analgesia diary. Ease of surgical exposure and complications will also be analysed.

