## Trial summary

This study aims to compare the effectiveness and efficiency of a standard medial parapatellar approach versus a sub-vastus approach in total knee replacement and to evaluate the clinical outcomes of care in each group. We propose a randomised controlled trial, with follow-up at 52 weeks, in a large sample population of 230 patients with patient based outcomes. The trial summary can be seen in figure 1. Patients will be recruited at their pre-operative assessment with randomisation taking place on their day of admission for surgery. Clinical and functional assessments will be carried out by a research nurse and physiotherapist respectively, pre and post-operatively, with the physiotherapist unaware of the approach taken. The primary outcome measure for the study is the Knee Society Score [12] and this will be collected at baseline and at 1, 6, 12 and 52 weeks post-operatively. Other outcome measures will include patient based (EuroQol 5D [10], WOMAC Index [11]), clinical (complications, blood loss, use of analgesia) and functional (range of motion) measures. Data will be analysed on an intention to treat basis with the principal comparisons being the mean difference in the Knee Society Score between the two groups at 1, 6, 12 and 52 weeks post-operatively.

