## Assessment of outcome

The primary outcome measure for this study will be the Knee Society Score [12] at 52 weeks, and will be carried out by a trained independent assessor (physiotherapist) who will be blinded to the surgical approach taken.

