### Secondary outcomes – patient based

1. EuroQol-5D [10]. A simple, generic measure of health outcome. It allows an accurate self-description of current health related quality of life, assessing mobility, self-care, usual activity level, pain/discomfort and anxiety/depression.

2. WOMAC Osteoarthritis Index [11]. An osteoarthritis specific measure of health outcome, assessing pain, stiffness and activity level.

3. SF-36 [13]. A comprehensive generic measure of health outcome.

4. Time to normal activities/return to function (days/weeks)

5. Pain (7 day pain diary – visual analogue scale 0–100)

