### Data analysis

Intention to treat analysis – all patients entered into the trial will be followed up in the group to which they were randomly allocated regardless of which treatment they received. Continuous data will be analysed using repeated measures analysis of variance while the chi square test will be used to compare all categorical data. Baseline characteristics of the group will be compared using appropriate parametric and non parametric tests to ensure balance has been achieved with randomisation.

The principal comparisons will be between:

a) Comparison of the mean total Knee Society Score between the two groups at 1, 6, 12 and 52 weeks post-operatively.

b) Comparison of all secondary outcome measures between the two groups.

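### The abstract, outcome section and analysis section disagree on what is primary, while the sample size rests on the 1-year Knee Society Score alone

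*Protocol article*

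**What the plan says.** Five places in the article bear on what is primary.

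- **Abstract, Methods:** "The primary outcome measures will be the American Knee Society and WOMAC Scores". EuroQol and SF-36 are named there as the secondary measures. The abstract lists the visits for all outcomes but does not pick one as primary.
- **Trial summary:** the Knee Society Score alone is primary, and WOMAC is among the other measures. The analysis is described as "the principal comparisons being the mean difference in the Knee Society Score between the two groups at 1, 6, 12 and 52 weeks".
- **Assessment of outcome:** "The primary outcome measure for this study will be the Knee Society Score [12] at 52 weeks". The list that follows, Secondary outcomes – patient based, includes "WOMAC Osteoarthritis Index [11]. An osteoarthritis specific measure of health outcome".
- **Sample size:** one comparison of the 1-year Knee Society Score, two-sided 5%, 90% power, 105 per group.
- **Data analysis:** the principal comparisons are (a) the mean total Knee Society Score at the four post-operative visits and (b) "Comparison of all secondary outcome measures between the two groups". Continuous data go into a repeated measures analysis of variance, with no term or contrast singled out.

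The section on interim analyses adds that the first monitoring analysis of the primary endpoint takes place once 50 patients have completed their 1-week assessment, with a nominal stopping level of p <= 0.02.

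**The concern.** Which result is the trial's primary result depends on the section the reader follows. Under Assessment of outcome it is the 52-week score. Under the abstract, WOMAC shares that status. Under Trial summary and Data analysis, a 1-week, 6-week or 12-week difference stands level with the 52-week one. Once Data analysis includes every secondary outcome, the label principal sets no priority at all.

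The choice matters in this trial. The Background reports mainly early benefits of the sub-vastus approach and says longer follow-up is needed to learn whether they last. An early gain with no difference at one year is a foreseeable outcome. Trial summary and Data analysis would let it be reported as a principal finding; Assessment of outcome would not. Unless the text is settled beforehand, the choice can be made after the data are seen.

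**Working it through.** **1. What the sample size was built for.** Inputs from Sample size: mean 172.2, SD 20, a 5% increase, two-sided 5%, 90% power. The difference is 0.05 × 172.2 = 8.61 points. The normal formula is n per group = 2 × (z for 1 − α/2 + z for power)² × (SD/difference)².

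- Difference 8.61: 2 × (1.960 + 1.282)² × (20/8.61)² gives 114 per group, not the stated 105.
- Difference rounded up to 9: 104 by the normal formula, 104.7 (so 105) by the t-test. This is the only variant tried that returns the stated figure.
- Allowance for loss: 105 × 1.10 × 2 = 231, as stated.

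The gap between 105 and 114 is a separate matter. What counts here is that the calculation contains one outcome, one time point and one undivided 5% level. It therefore fits Assessment of outcome and none of the wider descriptions.

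**2. What the wider descriptions would need if each were confirmatory.** Same formula, difference 8.61, SD 20, 90% power, Bonferroni split:

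- Four visits, α = 0.05/4 = 0.0125: 155 per group. With 105 per group, power is 73%.
- Knee Society Score and WOMAC at one visit, α = 0.05/2 = 0.025: 134 per group. With 105, power is 81%. This assumes the same standardised effect for WOMAC, for which the article gives no figure.

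For comparison, 105 per group at an undivided 5% gives about 88% power at a difference of 8.61.

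**3. False-positive chance if a win at any of the four visits counted as success.** With independent tests it is 1 − 0.95⁴ = 0.185. With equally correlated normal test statistics (simulation, 1,000,000 draws):

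- correlation 0.3: 17.4%
- correlation 0.5: 15.6%
- correlation 0.7: 13%
- correlation 0.9: 9.3%

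The article gives no between-visit correlation, so these are assumed values. Repeated scores on the same knee will not be independent, so 18.5% is an upper bound rather than an expectation.

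**4. The interim look.** A primary endpoint at 52 weeks cannot be monitored from 1-week assessments. If recruitment were even over the planned 12 months (an assumption), the 50th of 231 patients would enter at about 50/231 × 12 = 2.6 months, when nobody could have 52-week data. The rule works only if the 1-week score is treated as the primary endpoint, which contradicts Assessment of outcome.

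**The case against.** The strongest reply is that the article does contain a controlling definition. Assessment of outcome is the section meant to define the outcome, Sample size agrees with it, and Trial summary names the same single instrument. Collecting a score at four visits is compatible with fixing its primary time point at 52 weeks. On this view the only conflict over the instrument is in the abstract, and the remainder is loose use of the word principal. A repeated measures model could also supply one overall group test rather than four.

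Part of this stands. Trial summary and Assessment of outcome agree on the instrument, and the abstract does list visit times. A multiplicity rule may also sit in an analysis plan that is not shown, so its absence here is not held against the article.

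What does not stand is that the definition controls. Nothing gives it precedence, and Data analysis, which governs the comparisons, departs from it. Dropping the abstract would still leave Trial summary, Data analysis and the interim section out of line with Assessment of outcome and Sample size. Nor does an overall group term settle the matter: averaged over visits, it is not the 52-week difference for which the trial was sized.

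A reader might go further and infer that the 5% error rate behind the sample size is broken. The documents do not support that. The 52-week comparison keeps its own 5% whatever else is tested, and no section says that success on any comparison counts as trial success.

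**Conclusion.** The inconsistency is real and lies in the current text; it is not detail deferred to an analysis plan. Two features of the primary outcome are unsettled: whether WOMAC shares primary status (the abstract against Trial summary and the secondary list), and whether the principal comparison is one visit or four (Assessment of outcome and Sample size against Trial summary and Data analysis). Listing all 14 secondary items (5 + 6 + 2 + 1 across the four secondary lists) as principal removes any ranking.

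The size depends on how the text is used. If the 52-week score alone is confirmatory, no multiplicity inflation arises. If any of the four visits could carry the claim, the false-positive chance is roughly 9% to 18.5%. That range rests on separate 5% tests, an any-win rule that the article does not state, and assumed correlations from 0.9 to 0. It shows what the ambiguity permits, not the error rate of the plan.

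**What to change.** State once that the sole primary outcome and the sole principal comparison is the total Knee Society Score at 52 weeks. Specify the test as the 52-week between-group contrast from the repeated measures model, at two-sided 5% less any level spent at the interim look. Then:

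- align the abstract, Trial summary and Data analysis with that statement;
- label the scores at 1, 6 and 12 weeks, WOMAC at every visit and all other outcomes as secondary;
- delete item (b) from the principal comparisons in Data analysis;
- reconcile the interim section with the 52-week definition, saying which outcome is examined after the 1-week assessments and in what capacity.

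This is wording only. It adopts a definition already in the article, and resolving the multiplicity this way needs no added patients. The price is that neither an early visit nor WOMAC can be claimed as the primary success.

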**Discussion:**

Evidence is lacking concerning the best surgical approach to the knee joint for patients undergoing primary total knee replacement. This pragmatic randomised trial tests the hypothesis that the sub-vastus approach is significantly superior to the standard medial parapatellar approach in terms of short and long term knee function.

## Background

There is general agreement about the value of knee replacement surgery, with approximately 30,000 knee replacements performed annually in the UK. However, there is uncertainty as to the best surgical approach to the knee joint.

Total knee replacements through a standard medial parapatellar arthrotomy [1] are routinely carried out. The sub-vastus (southern) arthrotomy has been suggested as an alternative [2]. There have been two previous published trials of the sub-vastus approach versus a standard medial parapatellar approach.

In the first of these [3], 20 patients undergoing bilateral knee arthroplasty were studied, with follow-up at 1, 4 and 12 weeks post-operatively. The patients whose knee was approached by the sub-vastus method showed 35% and 16% greater quadriceps strength at 1 week and 1 month respectively. In addition, the authors highlighted several anatomical advantages. The approach maintains the medial parapatellar blood supply and preserves the extensor mechanism [4-6]. Thus, theoretically, it decreases the likelihood of patellar subluxation, fracture, or patellar avascular necrosis (reported as having an incidence of 17%, 21% and 10% respectively) [7,8].

In the second of these trials [4], 41 consecutive primary knee arthroplasties were studied with follow-up at 6 months. Patients who had the sub-vastus approach were able to straight leg raise 4 days sooner (p = 0.008) and used 40% less post-operative analgesia (p = 0.05). They also spent on average 3 days less in hospital (p = 0.01).

The subvastus approach has also been reported to have decreased wound complications, a shorter hospital stay, a reduction in analgesia usage and an early return to function when compared to the standard median parapatellar approach [2,4,9].

There were problems with the validity and quality of both studies, as they were not truly randomised, and involved only a small number of patients and follow-up was short. Long term follow-up is needed to determine whether potential short term benefits increase long term effectiveness. A larger sample size will allow a wider range of outcomes to be investigated (in particular knee function) and a broader range of patients to be recruited to improve external validity and allow for sub-group analysis (e.g. by age and sex). Furthermore, involving more surgeons will allow assessment of variation in outcome by individual surgeons.

We propose, therefore, a fully randomised controlled trial, with long-term follow-up, in a large sample population with patient-based outcomes to compare the standard approach with the sub-vastus approach in total knee replacement.

## Objectives

This trial proposes to:

1. study the effectiveness and efficiency at 1, 6, 12 and 52 weeks of a standard medial parapatellar arthrotomy compared with a sub-vastus arthrotomy in primary total knee replacement.

2. examine both clinical and economic outcomes of care of a standard medial parapatellar arthrotomy compared with a sub-vastus arthrotomy in primary total knee replacement at 1, 6,12 and 52 weeks.

3. examine patient based outcomes of care (EuroQol [10], WOMAC [11], pain (visual-analogue scale)) of a standard medial parapatellar arthrotomy compared with a sub-vastus arthrotomy in primary total knee replacement at 1, 6,12 and 52 weeks.

## Trial summary

This study aims to compare the effectiveness and efficiency of a standard medial parapatellar approach versus a sub-vastus approach in total knee replacement and to evaluate the clinical outcomes of care in each group. We propose a randomised controlled trial, with follow-up at 52 weeks, in a large sample population of 230 patients with patient based outcomes. The trial summary can be seen in figure 1. Patients will be recruited at their pre-operative assessment with randomisation taking place on their day of admission for surgery. Clinical and functional assessments will be carried out by a research nurse and physiotherapist respectively, pre and post-operatively, with the physiotherapist unaware of the approach taken. The primary outcome measure for the study is the Knee Society Score [12] and this will be collected at baseline and at 1, 6, 12 and 52 weeks post-operatively. Other outcome measures will include patient based (EuroQol 5D [10], WOMAC Index [11]), clinical (complications, blood loss, use of analgesia) and functional (range of motion) measures. Data will be analysed on an intention to treat basis with the principal comparisons being the mean difference in the Knee Society Score between the two groups at 1, 6, 12 and 52 weeks post-operatively.

**Figure 1 F1:**
[figure not shown]
Flow Chart.

## Design

### Study type

Randomised controlled trial comparing standard medial parapatellar arthrotomy with a sub-vastus arthrotomy in total knee replacement.

### Participants

Participants will be patients undergoing primary bi (tibial-femoral joint) or tri (tibial-femoral-patellar) compartmental knee replacement for any indications. These patients will be recruited from North Staffordshire Hospital, Stoke on Trent.

## Treatment details

A Low Contact Stress knee prosthesis manufactured by Depuy will be used. Both consultant orthopaedic surgeons and consultant-supervised Orthopaedic Specialist Registrars will be eligible to perform each of the approaches.

### Skin incision

The prosthesis will be inserted via a mid-line skin incision beginning over the medial portion of the quadriceps tendon, four inches above the upper border of the patella. The incision will continue in a gentle curve following the medial margin of the quadriceps tendon, patella and patella tendon. It will then cross the upper end of the tibia and end inferior to the tubercule of the tibia. Exposure of the knee joint will then occur either by a standard medial parapatellar arthrotomy [1] or sub-vastus arthrotomy [2].

### Standard medial parapatellar approach

A straight incision will be made through the three layers of fascia over the quadriceps and the patella tendons. The synovia and deep aponeurosis will be divided medial to the patella and the quadriceps tendon will be separated in the line of its fibers just lateral to the insertion of the vastus medialis. The patella tendon will be freed along its medial border to the level of the tibial tubercule, exposing the infrapatellar bursa. The patellar will be dislocated laterally.

### Sub-vastus approach

Fascia layer I will be incised inline with the mid-line skin incision. At the level of the patella, it will be incised slightly medially. Beginning proximally, the fascia layer I will be raised off the perimuscular fascia of the vastus medialis down to its insertion site. The inferior edge of the vastus will be lifted off the periosteum and intermuscular septum with blunt finger dissection for approximately 10 cm proximal to the adductor tubercle. The tendinous insertion of the vastus medials will be incised about midpatella. Care will be taken not to incise the synovium. Lifting the extensor mechanism anterior and lateral will allow a curvilinear medial arthrotomy beginning in the suprapatellar pouch and ending at the tibial tubercule. Sharp soft tissue release from the proximal tibia will be performed. The patella will be everted laterally with the knee in full extension. The knee will be flexed while the vastus medialis will be bluntly dissected off intermuscular septum proximally. If a lateral release is needed, it will be carried out from the outside in, with the knee in full flexion.

## Eligibility

A patient will be eligible if:

(i) They require a bi or tri compartmental knee replacement

(ii) They require a unilateral knee replacement

(iii) They have given their informed consent

(iv) The surgeon has no clear preference for either of the approaches

A patient will be ineligible to enter the trial if:

(i) They need a revision knee replacement

(ii) They have had, or will require a major arthrotomy in the other knee in a 12 month period

(iii) They have had previous open surgery in or around the knee in the previous 12 months e.g. high tibial osteotomy, femoral osteotomy, ORIF for fracture, patellar realignment, patellectomy and open meniscectomy.

(iv) They require a bi-lateral knee replacement at a single visit

(v) They have a valgus angle of ≥ 20°

## Recruitment

Patients will be recruited over a 12 month period. Surgical lists will be reviewed weekly to identify all patients referred to the participating hospital centre and listed for total knee replacement. Their notes will be screened prior to their pre-operative outpatient appointment. At their pre-operative visit patients will be informed of the nature of the study by their consultant surgeon. Eligible patients will be provided with an information leaflet explaining the nature of the study to them. They will be invited to ask questions regarding the research. Patients will then be asked to return home and think about whether or not they wish to participate. During the 4–6 week period following their pre-operative visit and prior to admission for surgery, patients will be contacted by the research nurse to discuss their participation in the study and to address any unanswered questions they may have. On the day of admission, the patients will have a further opportunity to discuss participation with the research nurse involved in the trial. Those patients wishing to take part will be invited to sign an informed consent form by their surgeon. Following consent being obtained, patients will be randomised on their day of admission to either a sub-vastus or medial parapatellar approach.

## Randomisation

Patients will be randomised according to a minimisation method using a telephone randomisation service. The minimisation variables will be surgeon, and gender. Randomisation will take place after informed consent will have been given, eligibility criteria will have been checked, and baseline measurements will have been taken. The randomisation will take place on the day of admission. This will be carried out at the co-ordinating centre. At this telephone call, basic descriptive information will be given (patient's name, sex, date of birth, hospital and surgeon). After this phone call, the patient will be considered irrevocably to have entered in the trial for the purposes of the research.

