## Statistical considerations

### Sample size

In a group of 86 patients undergoing total knee arthroplasty the mean 1 year post-operative Knee Society Score was 172.2 with a standard deviation of 20 and a range of 98–200 [14]. To detect a 5% increase in the post-operative Knee Society Score in the sub-vastus group compared to the medial parapatellar group with a two sided significance level of 5% and a power of 90% a sample size of 105 patients would be required in each group. An additional 10% will be recruited to each group to allow for any patients lost to follow-up, giving a total sample size of 231.

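### The stated analysis names no adjustment for baseline Knee Society Score, surgeon or gender, and it prescribes baseline significance tests that cannot ensure balance

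*Protocol article*

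**What the plan says.** The Randomisation section of the protocol article states: "The minimisation variables will be surgeon, and gender". It also says that baseline measurements come before randomisation, and that sex and surgeon are given in the randomisation call. Of the Knee Society Score, the Trial summary says "this will be collected at baseline and at 1, 6, 12 and 52 weeks post-operatively". All three variables are therefore on file by the time a patient is allocated.

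The Data analysis section says: "Continuous data will be analysed using repeated measures analysis of variance while the chi square test will be used to compare all categorical data". Its principal comparison is of mean total Knee Society Score between the groups at the four post-operative visits. It names no baseline covariate and no surgeon or gender term. The one use it gives for baseline data is this: "Baseline characteristics of the group will be compared using appropriate parametric and non parametric tests to ensure balance has been achieved with randomisation".

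The Background expects outcome to vary between surgeons, and Treatment details allows both consultants and supervised registrars to operate.

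**The concern.** The allocation treats surgeon and gender as worth balancing, and the primary outcome is measured before surgery, yet the stated analysis uses none of this. Two different costs follow, and they should be kept apart.

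- **Baseline score.** It is not a minimisation factor, so only chance controls its balance. Leaving it out gives a valid standard error that is larger than it need be.
- **Surgeon and gender.** Minimisation balances them, so the treatment estimate varies less than an unadjusted model assumes. If they are prognostic, the model standard error is too large and the test rejects a true null less often than 5%.

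The baseline tests are a separate fault, and one that the article states outright. Under proper randomisation the null hypothesis of such a test is true by design, so a significant result is a false alarm. A non-significant result does not remove the effect of whatever imbalance is present. Testing therefore cannot do the job the article gives it.

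**Working it through.** **Inputs from the Sample size section.** The reference data are "the mean 1 year post-operative Knee Society Score was 172.2 with a standard deviation of 20 and a range of 98–200". The target is "To detect a 5% increase in the post-operative Knee Society Score in the sub-vastus group", that is 0.05 × 172.2 = 8.61 points. The test is two-sided at 5%, with "a power of 90% a sample size of 105 patients would be required in each group".

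**Inputs not in the documents, so assumed as ranges.** These are the correlation r between baseline and 52-week score, and the share R² of outcome variance explained by surgeon and gender.

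**Step 1: the plan's own figure.** n per group = 2 × (1.960 + 1.282)² × (20 / 8.61)² = 113.4, so 114 rather than 105. A rounded 9-point difference gives 104 (105 by the t-test version), but 9 is not 5% of 172.2. At 105 per group the standard error is 20 × √(2/105) = 2.760. Power is Φ(8.61/2.760 − 1.960) = Φ(1.159) = 87.7% (87.4% by t-test). The shortfall from 90% is a separate sample-size matter. It is used here only as the starting point.

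**Step 2: baseline adjustment.** The residual SD is 20 × √(1 − r²). For a single-visit comparison at 52 weeks with a difference of 8.61:

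| r (assumed) | Residual SD | Power at 105 per group | n per group for 90% |
|---|---|---|---|
| 0 | 20.00 | 87.7% | 114 |
| 0.2 | 19.60 | 88.9% | 109 |
| 0.3 | 19.08 | 90.5% | 104 |
| 0.4 | 18.33 | 92.6% | 96 |
| 0.5 | 17.32 | 95.0% | 86 |

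The last column shows the gain without relying on the figure of 105.

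**Step 3: omitting the minimisation factors.** With the factors balanced, the true SD of the estimate is 2.760 × √(1 − R²), while an unadjusted model still reports 2.760. The standard error is overstated by 1/√(1 − R²) − 1. The true type I error is 2 × [1 − Φ(1.960/√(1 − R²))].

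| R² (assumed) | SE overstated by | True type I error | Power unadjusted | Power adjusted |
|---|---|---|---|---|
| 0.05 | 2.6% | 0.044 | 88.3% | 89.3% |
| 0.10 | 5.4% | 0.039 | 88.9% | 90.8% |
| 0.20 | 11.8% | 0.028 | 90.3% | 93.7% |

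**Step 4: simulation.** Minimisation of 210 patients was simulated with 2,000 repetitions per scenario. Six surgeons and a 0.8 biased coin were assumed.

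- R² = 0.10, r = 0.3: the mean unadjusted model standard error was 2.76 against a true SD of about 2.65, with type I error 0.044.
- R² = 0.20, r = 0.3: 2.76 against about 2.45, with type I error 0.028.
- R² = 0.05: the unadjusted type I errors of 0.054 and 0.041 cannot be told apart from 5%, since the simulation error is about √(0.05 × 0.95/2000) = 0.005.
- The analysis adjusted for baseline, gender and surgeon had type I error between 0.040 and 0.056, and higher power in every scenario (for example 93.3% against 88.8% at R² = 0.10, r = 0.3).

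**Step 5: the baseline tests.** With k independent tests at 5%, the chance of at least one false alarm is 1 − 0.95^k, which is 40% for k = 10. The article does not say how many variables will be tested, and correlation between them would change the figure.

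**The case against.** The strongest reply is that the point on covariates rests on silence. This is a condensed article, its analysis plan is not shown, and a covariate list is ordinary content for such a plan. Repeated measures analysis of variance can carry baseline, surgeon and gender terms, and nothing in the article rules them out. This stands in part. A reader might infer that the trial ignores these variables, or that it means the baseline tests to replace adjustment. The documents support neither: they name no adjustment, and they do not present the tests as a substitute or as a trigger for it. What remains is that the article does fix a method, and a better one is available from data already collected. The sentence on baseline tests is explicit and no unseen plan explains it.

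A reader might also infer that the standard error is wrong in general, or that false positives are at risk. Neither follows. Only omission of the minimisation factors affects the validity of the standard error, only if they are prognostic, and the error is conservative.

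Nor does a chance baseline imbalance pass into the estimate in full. It carries over in proportion to the baseline-outcome slope. At r = 0.5, an imbalance of one standard error moves the estimate by 0.5 × 2.760 = 1.4 points, and the unadjusted standard error already allows for such variation.

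The size of the gain is also open to challenge. The reference scores run up to 200, only (200 − 172.2)/20 = 1.4 SD above the mean, and down to 98, which is 3.7 SD below. That suggests bunching at the top, so a weak correlation is plausible, and at r = 0.2 the gain is about one point of power. The figures are also for one visit and not for the full repeated measures model. Both limits stand.

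**Conclusion.** The point holds as an improvement to the stated method. The Data analysis section names no adjustment for baseline score, surgeon or gender, and its baseline significance tests cannot serve their stated purpose.

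The size depends on two quantities that the documents do not give. The gain from baseline adjustment at 105 per group runs from about one point of power at r = 0.2 to about seven at r = 0.5, and an r of 0.3 would bring power back to 90%. The cost of omitting surgeon and gender is nil if they are not prognostic. All of this takes an SD of 20 in both groups and a single comparison at 52 weeks. The unadjusted analysis would not be invalid. It would be less precise, and somewhat conservative if the minimisation factors matter.

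**What to change.** In the Data analysis section:

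- Specify the 52-week Knee Society Score comparison as a model adjusted for baseline score, gender and surgeon. Do the same for the other continuous outcomes measured at baseline, each with its own baseline value.
- Define surgeon as the entry used in the minimisation call, because consultants and supervised registrars may both operate. Fit it as a random effect if numbers per surgeon are small.
- Allow sparse binary outcomes, such as complications, to omit surgeon.
- Present baseline data descriptively by group and delete the baseline significance tests.

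The cost is a change of wording plus the decision on how surgeon is coded. No extra patients or data are needed, since all the variables are recorded by the time of randomisation. The change should be made before outcome data are seen by group.
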